## 6.5 Safety Analysis

Safety analyses will involve examination of the incidence, severity, and type of treatment‑emergent AEs reported, and changes in vital signs and laboratory test results from baseline (Day 0 pre-dose) to specified time points throughout the study.

### 6.5.1 Adverse Events

Treatment-emergent AEs reported during the study will be coded using the MedDRA dictionary. An AE will be summarized by dose group and the following:

- System organ class and preferred term
- System organ class and severity
- System organ class, preferred term, and severity

These summaries will be presented for the following subsets:

- All AEs
- Drug-related AEs
- AEs resulting in discontinuation of study drug or the study
- SAEs, including deaths

Hypoglycemic events will be summarized descriptively, with summaries provided for the subsets of all hypoglycemic AEs and all severe hypoglycemic AEs.

For tables classifying AEs by severity, if a subject has multiple occurrences of an AE with the same MedDRA term, the most severe event will be chosen.

A summary and by-subject listing will be provided for any subject who died, experienced SAEs, or experienced AEs resulting in discontinuation of study drug or the study.

Non‑treatment-emergent AEs will not be summarized.

### 6.5.2 Clinical Laboratory Evaluation

Clinical laboratory results will be tabulated. Values outside of the normal ranges will be identified and reported.

### 6.5.3 Vital Signs

For each assessment of vital signs, changes in vital signs from baseline (Day 0 pre-dose) will be summarized. Vital signs (including include pulse, blood pressure [systolic/diastolic], respiratory rate, temperature [oral or tympanic]), p02, body weight, height, and BMI will be summarized by treatment group and assessment time.

## 6.6 Missing Data

Safety results will be summarized using all available data. Multiple attempts will be made to obtain missing data. If there is missing data affecting the primary endpoint, a sensitivity analysis using last observation carried forward (LOCF) will be conducted.

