# 1.0 background

## 1.1 Overview

The role of IL-6 in regulating glucose homeostasis is unclear and the ongoing debate is characterized by IL-6 being a “bad or a good guy”. In support of the bad guy hypothesis systemic IL-6 levels are elevated in obese individuals and in patients with type 2 diabetes, and these elevated IL-6 levels predict disease development (1; 2). In addition, IL-6 induces insulin resistance in liver and fat tissues (3). The discovery that skeletal muscle produces and releases IL-6 in response to muscle contraction (exercise) has challenged the bad guy hypothesis, in addition, the fact that IL-6 improves muscle insulin sensitivity (3) supports a potential beneficial role of IL-6 in regulating glucose homeostasis. We have recently observed that IL-6 induces GLP-1 production and release from intestinal L-cells and islet -cells (Ellingsgaard et al., manuscript in preparation), indicating that IL-6 may play an important beneficial role in regulating glucose homeostasis.

It has been shown recently that IL-1 antagonism improves glycemia and insulin secretion in patients with type 2 diabetes (4). However, IL-1 antagonism also decreases IL-6 levels in auto-inflammatory diseases including type 2 diabetes. Subsequently, IL-1 antagonism could possibly decrease GLP-1 levels and thereby reduce the beneficial effect of IL-1 antagonism on glucose-metabolism.

Exercise improves -cell function but the underlying mechanism is unclear. Since muscle contraction leads to a strong increase in circulating IL-6 (5), we hypothesize that exercise-induced IL-6 promotes GLP-1 secretion from intestinal L-cells and islet α-cells, thereby providing a mechanism how physical activity (exercise) can help maintain and improve -cell function in obese individuals and patients with type 2 diabetes.

However, little is known about the regulation of muscle derived IL-6 during exercise and in particular whether it is regulated by IL-1 or independently of the IL-1 system. The presence of high levels of IL-1α in the muscle makes it a candidate for IL-6 regulation.

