# 3.0 Study Design

## 3.1 Description of the Study

This is a randomized placebo-controlled, double blind, cross-over, proof-of-concept study of the effects of IL-1 antagonism on peripheral muscle physiology.

The study will consist of one screening visit followed by 3 study visits. During the first two study visits, the subjects (20 apparently healthy, lean men) will perform a submaximal exercise bout on a treadmill for 60 minutes. In addition, subjects will fill in an Activity Induced Fatigue (ACTIF) Scale before (ACTIF pre) and 3-4 hours after (ACTIF post) exercise. After every ACTIF Scale evaluation the subjects perform a Hand-Grip-Strength-Test, assessing the actual motoric shape. Then the subjects are tested by a neuropsychologist by applying the Symbol Digit Modalities test (SDMT), a cognitive screening-test to assess information processing speed and working memory. To assess depression, subjects will be examed by the Beck-Depression-Inventory Fast Screen (BDI-FS), a short version of the Beck-Depression-Inventory (BDI), depicting different facets of depression. These additional tests are performed to evaluate the impact of fatigue on cognitive, motoric and emotional behavior. Before the Activity Induced Fatigue (ACTIF) Scale after exercise (ACTIF post) is applied, subjects will be asked to evaluate their general, motoric and cognitive condition using the Visual analogue scale (VAS) Fatigue after exercise. Subjects will be randomly assigned into two groups consisting each of 10 subjects receiving study medication in a double-blinded, crossed over manner. Treatment consists of a single subcutaneous injection of 100mg IL-1Ra or placebo at visit 1 and 2.,

[visit 1: IL-1Ra/ placebo; visit 2: placebo/ IL-1Ra (cross-over to day 1);]. See table 1 on page 18.

Additionally the vascular function will be evaluated before the injection of the study medication and 1 hour after the exercise bout. The large arterial stiffness known as cardio ankle vascular index (CAVI) and the pulse wave velocity (PWV) will be measured by an oscillometric sphygmograph (Vasera). Furthermore the small vessels will be examined by taking a picture from the retina to calculate the arteriolar-to-venular-ratio (AVR). To assess overall activity of the participants will be given an activity questionnaire (Aktivitätsfragebogen) at screening (12).

The screening visit and the three study visits will be separated by at least 72 hours and at most 9 days.

.

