## 3.5 Enrollment, Treatment Assignment, Blinding, and Unblinding

### 3.5.1 Enrollment

Once Screening is completed and subject eligibility is confirmed, a subject will be assigned a subject number and a kit number(s) according to the randomization schedule.Enrolled subjects who discontinue the trial prior to receiving study drug will be replaced. Subjects who discontinue after receiving any amount of study drug will not be replaced (see Section 4.3.1).

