## 3.8 Outcome Measures

### 3.8.1 Primary Outcome Measure

The primary endpoint is change in exercise-stimulated IL-6 between group dosed with placebo and anakinra.

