### 3.8.2 Secondary Outcome Measures

The secondary endpoints are as follows:

- Change in glucose metabolism, insulin glucagon and GLP-1 secretion due to any treatment.
- Change of inflammatory markers (CRP, TNFα, IL-1Ra) due to any treatment.
- Change of stress hormones (cortisol, growth hormone, catecholamines) due to any treatment.
- Change of muscular enzymes (CK) due to any treatment.
- Well-being during and after exercise including muscle soreness due to any treatment.
- Activity Induced Fatigue (ACTIF) Scale before and after exercise due to any treatment.
- Depression
- Cognition
- Motor strength
- Change of vascular function (CAVI, PWV and AVR) due to any treatment.

The tests used to investigate the regulation of IL-6 during exercise are summarized in Table 3.

Table 3
Bloodanalysis

Blood samples will be drawn at the following time points: -60 min before, 0, 10, 20, 30, 40, 50, 60 min during exercise and at +10, +20, +30 and + 60 min after exercise.

A total of 250 ml blood will be drawn throughout the study.

The following parameters will be assessed:

| Time points: | -60 | 0 | 10 | 20 | 30 | 40 | 50 | 60 | +10 | +20 | +30 | +60 |
| --- | --- | --- | --- | --- | --- | --- | --- | --- | --- | --- | --- | --- |
|  | **before** | **exercise** | | | | | | | **after** | | | |
| IL-6 | x | x | x | x | X | x | x | x | x | x | x | x |
| GLP-1 (active) | x | x | x | x | X | x | x | x | x | x | x | x |
| Glucagon | x | x | x | x | X | x | x | x | x | x | x | x |
| Insulin | x | x | x | x | X | x | x | x | x | x | x | x |
| Glucose | x | x | x | x | X | x | x | x | x | x | x | x |
| IL-1Ra | x |  |  | x |  | x |  | x | x |  | x |  |
| GIP | x |  |  | x |  | x |  | x | x |  | x |  |
| usCRP | x |  |  | x |  | x |  | x | x |  | x |  |
| TNF-a | x |  |  | x |  | x |  | x | x |  | x |  |
| Cortisol | x |  |  | x |  | x |  | x | x |  | x |  |
| GH | x |  |  | x |  | x |  | x | x |  | x |  |
| CK | x |  |  |  |  |  |  | x |  |  |  | x |

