# 6.0 Data Analysis and Statistical Methods

Data will be analyzed for safety and biological endpoints. Safety analyses will include all subjects who received any amount of study drug. Efficacy analyses will include all randomized subjects. Analyses of the population of subjects who completed treatment may also be performed.

Since the sample size is small, only exploratory statistical testing will be performed. Study results will be summarized using primarily descriptive statistics and 95% confidence intervals. Since this is a proof of concept study, evaluating an issue that has never been examined before, it is not possible to perform a power calculation.

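### Section 6.6 sets LOCF as the sensitivity analysis for missing IL-6, but it does not suit a serial exercise curve in a two-period crossover and cannot test robustness

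*Protocol*

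**What the plan says.** The primary endpoint (section 3.8.1) is the treatment difference in exercise-stimulated IL-6, with no summary measure fixed. Section 3.8.2, Table 3, has 12 IL-6 samples per bout: one at -60 min, seven from 0 to 60 min at 10-minute steps, and four at +10, +20, +30 and +60 min. Section 1.1 gives the expected shape: "Since muscle contraction leads to a strong increase in circulating IL-6 (5". Sections 3.1 and 3.5.2 describe a two-period crossover, so each man has one visit per treatment.

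On missing data, section 6.6 has one statement for the primary endpoint: "If there is missing data affecting the primary endpoint, a sensitivity analysis using last observation carried forward (LOCF) will be conducted". Its other analysis rule is limited to safety: "Safety results will be summarized using all available data". It does not say whether the carrying runs only within a visit or also from Visit 1 to Visit 2.

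Two further rules matter here. Section 3.5.1 states: "Subjects who discontinue after receiving any amount of study drug will not be replaced". Section 6.0 states: "Efficacy analyses will include all randomized subjects", and makes an analysis of completers optional. A missed Visit 2 would therefore normally stay missing while the man remains in the efficacy set.

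**The concern.** LOCF assumes that IL-6 would have stayed flat after the last sample. During the run this contradicts the protocol's own premise. If a catheter fails or a run stops early, the missing higher values are replaced by a lower one, and the end-of-exercise IL-6 at that visit looks reduced, which is the effect under study.

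For a man with no Visit 2, the only earlier post-dose IL-6 values were taken under the other treatment. If they are carried over, his anakinra-placebo difference is exactly zero and counts as an observation. Shrinkage is not a safe error here: the synopsis hypothesis sets regulation by IL-1 against independence from it, so a pull towards zero favours one of the two answers.

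A sensitivity analysis should show whether the main result survives a different, credible assumption about the missing values. If the analysis brings in its own error, neither agreement nor disagreement with the main result can be interpreted.

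**Working it through.** The protocol states no figure for this point that could be reproduced. It gives no fold rise, no post-exercise course, no sample-loss rate and no dropout rate. These are assumed below and shown as ranges. From the protocol come the sampling times (Table 3) and the 20 subjects.

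**1. End-of-exercise value, samples lost after 40 min.** Let IL-6 rise from 1 at 0 min to g at 60 min.

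- Linear rise: the 40-min value is 1 + 2(g-1)/3, so the understatement is 1 - [1 + 2(g-1)/3]/g.
- Exponential rise: the 40-min value is g^(2/3), so the understatement is 1 - g^(-1/3).

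| g | Linear | Exponential |
|---|---|---|
| 3 | 1 - 2.333/3 = 22% | 1 - 0.693 = 31% |
| 5 | 1 - 3.667/5 = 27% | 1 - 0.585 = 42% |
| 10 | 1 - 7/10 = 30% | 1 - 0.464 = 54% |

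**2. Incremental AUC, 0-120 min, samples lost after 40 min.** For a linear rise, work in units of (g-1) x min, so the result does not depend on g.

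- LOCF area: 40 x (2/3)/2 + 80 x (2/3) = 13.3 + 53.3 = 66.7.
- True area, plateau after exercise: 30 + 60 = 90. 66.7/90 = 0.74, so 26% understated.
- True area, linear fall halfway to baseline by +60: 30 + 45 = 75. 66.7/75 = 0.89, so 11% understated.
- True area, linear fall fully to baseline by +60: 30 + 30 = 60. 66.7/60 = 1.11, so 11% overstated.

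For an exponential rise, by the trapezoid rule at the protocol's sampling times, the understatement for g = 3, 5, 10 is 38%, 44%, 52% with a plateau. With a full fall it is only 4% (g = 3) to 22% (g = 10).

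**3. Samples lost after the 60-min sample.** The end-of-exercise value is then unaffected. With a linear rise the LOCF area is 30 + 60 = 90, against a true area of 90 (plateau), 75 (half fall) or 60 (full fall), that is 0%, 20% or 50% overstated. Taking both rise shapes together, the overstatement is 20-23% for a half fall and 50-60% for a full fall.

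**4. A missed Visit 2, if values are carried between visits.** The imputed visit equals the observed one, so the man's difference is 0. With k such men of 20, the expected mean difference is (20-k)/20 of the true effect, a shrinkage of k/20: 5% for one, 10% for two, 20% for four.

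The interval suffers too. In 100,000 simulated trials (normal paired differences, visits missing completely at random, k = 4), coverage of the nominal 95% interval was about 91%, 87% and 81% at standardized within-subject effects of 0.66, 1.0 and 1.5. Complete pairs kept about 95% coverage and were unbiased under the same assumption.

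**5. A missed Visit 2, if values are carried only within a visit.** There is no earlier post-dose value at that visit to carry. LOCF supplies nothing, and the largest gap in a crossover is left without any sensitivity analysis.

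**The case against.** The strongest reply is that LOCF here is only a sensitivity analysis, run only if primary-endpoint data are missing, in a study that section 6.0 calls exploratory and mainly descriptive. That stands. A reader might infer that the primary result rests on LOCF. The text does not say so, and the main handling of missing IL-6 may lie in an analysis plan that is not shown.

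A reader might also infer that 6.6 orders values to be carried from Visit 1 to Visit 2. It does not. With 12 samples per bout, carrying within a visit is an equally natural reading. What stands is that 6.6 leaves this open, and either reading fails for a missed visit.

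A third tempting inference is that LOCF errs in a known direction. That holds for the end-of-exercise value when samples are lost during the run. It does not hold for AUC, where the sign depends on when samples are lost and how IL-6 moves afterwards, and the documents give no post-exercise course.

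There are partial safeguards. Section 6.0 permits an analysis of completers, section 4.3.1 allows extra subjects where non-compliance threatens the analyses, and 6.6 calls for repeated attempts to recover data. None is a defined alternative to LOCF: the first is optional, the second discretionary, and the third cannot recover an undrawn sample. Finally, two or four missed second visits are illustrative, since no dropout rate is stated.

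**Conclusion.** The point holds as a fault in the choice and wording of the sensitivity analysis in 6.6. LOCF contradicts the rise that the protocol expects, and for a missed Visit 2 it either imputes a zero effect or does nothing. Loss after 40 min of an assumed 3- to 10-fold rise understates the end-of-exercise IL-6 by 22-54% at the affected visit. The AUC error runs from about 52% understated (10-fold exponential rise, plateau) to about 11% overstated (linear rise, full fall). Loss after the 60-min sample overstates AUC if IL-6 falls. If values cross visits, the mean effect shrinks by 5% for each missed Visit 2 among 20 men. These sizes rest on assumed curves and counts; the arithmetic itself is exact for those inputs, apart from the simulated coverage. The main estimate is not shown to be affected. The change should be made because it is cheap and because the present check would not be informative.

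**What to change.** Amend section 6.6 only; the methods named in 6.4 can stay.

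- State that no IL-6 value is carried from one visit to the other.
- Replace LOCF with a sensitivity analysis that fits a mixed model to all observed log IL-6 values, with terms for treatment, time, period and subject. A truncated curve then contributes what was measured and nothing is carried forward.
- Report a complete-pairs analysis beside it. Section 6.0 already allows an analysis of completers as an option; this makes it definite.
- Interpolate an isolated missing sample between its two neighbours on the log scale.

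The cost is a short rewording of 6.6 and minor programming. It needs no extra data and is best done before unblinding. The mixed model assumes that missingness depends only on what was observed, which should be said when it is reported.

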## 6.7 Interim Analyses

There is no formal interim analysis for this study.

## 6.8 Publication Policy

The study will be sought published in an international peer-reviewed journal with the TNIL6 Study Group as author. Both positive and negative results will be sought published.

# 7.0 quality control and quality assurance

## 7.1 Ethical Considerations – Overall Risk and Benefit

This study will be conducted in accordance with the ethical principles stated in the most recent version of the Declaration of Helsinki II and the applicable guidelines on good clinical practice, whichever affords the greater protection to the individual.

As mentioned IL-1 antagonism with anakinra has been widely used as part of clinical practice in rheumatoid arthritis in more than 100.000 patients (8,9). Adverse event rates did not statistically exceed control levels in placebo-controlled trials.

There are no further risks to this study, besides the already mentioned drug related ones.

For the subjects participating in this study there will be, apart from the financial compensation, no further benefit.

## 7.2 Informed Consent

The informed consent document will be signed by the subject or the subject’s legally authorized representative before the subject participates in the study. Signed consent forms will be maintained as part of the study file and will be available for verification at any time. A copy of the informed consent document will be provided to the subject or the subject’s legally authorized representative

## 7.3 Study Monitoring Requirements

The CTU will be monitoring this study. Authorized representatives of the national or local health authorities will be permitted to inspect or audit the facilities and records relevant to this study.

## 7.4 Disclosure of Data

Subject medical information obtained for this study is confidential, and disclosure to third parties other than those noted below is prohibited. Subject data will be identified by study, subject ID number and initials.

Upon the subject’s permission, medical information may be given to his or her personal physician or other appropriate medical personnel responsible for his or her welfare.

Data generated by this study must be available for inspection upon request by representatives of the appropriate national and local health authorities, and the EC for each study site, if appropriate.

## 7.5 Retention of Records

Records and documents pertaining to the conduct of this study, including CRFs, consent forms, laboratory test results, clinical notes, and medication inventory records, will be retained for 10 years

**(**Assessing individual HR-VO2 relationships and VO2max**)**

The VO2max test is performed on the screening visit (day -28 to -7).

The purpose of the VO2max test is to determine individual heart rate (HR)-VO2 relationships, VO2max and HRmax during treadmill running.

The results from this test will be used to determine the HR corresponding to 75% of VO2max at which the subject will run during the 1-hour running test at visits 1, 2 and 3.

The VO2max test will be performed on a treadmill ergometer using an online system allowing direct measurements of O2 uptake.

Prior to starting the test, the subject is informed about the procedure, and before starting to warm up, a heart rate monitor and mouthpiece are placed around the chest and in the mouth respectively.

The actual test contains two parts: 1) 6 min work-out intervals at various running speed (HR-VO2 relationship), and 2) all out incremental VO2max test).

The subjects start running for 6 min at 10 km/h, followed by a 2 min break, continues for 6 min at 12 km/h, 2 min break, 6 min at 14km/h, 2 min break and 6 min at 16 km/h. After the last 6 min running period, the individual has a 10 min break and then the all out incremental test starts. The subject starts running at 16km/h for 2 min, followed by an increase by 1km/h every min until exhaustion.

Appendix 2a Research Chart

|  | Pre-screening phone call | **Screen**  (Day -28 to -7) | **Visit 1**  (Day 0) | +24h | +48h | +72h | **Visit 2**  [Day 6 (+3 Days)] | +24h | +48h | +72h | **Visit 3**  [Day 12 (+6 Days)] |
| --- | --- | --- | --- | --- | --- | --- | --- | --- | --- | --- | --- |
|  |  |  |  |  |  |  |  |  |  |  |  |
| Inclusion/exclusion criteria | x | x |  |  |  |  |  |  |  |  |  |
| Informed consent |  | x |  |  |  |  |  |  |  |  |  |
| Demographics |  | x |  |  |  |  |  |  |  |  |  |
| Medical history |  | x | x |  |  |  |  |  |  |  |  |
| Concomitant medication |  | x | x |  |  |  | x |  |  |  | x |
| Physical examination[[1]](#footnote-2) |  | x |  |  |  |  |  |  |  |  | x |
| ECG |  | x |  |  |  |  |  |  |  |  |  |
| CBC |  | x |  |  |  |  |  |  |  |  | x |
| Serum chemistry[[2]](#footnote-3) |  | x |  |  |  |  |  |  |  |  | x |
| Vital signs |  | x | x |  |  |  | x |  |  |  | x |
| Measurements of R thigh and R arm |  | x |  |  |  |  |  |  |  |  |  |
| Treadmill ergometer |  | x |  |  |  |  |  |  |  |  |  |
| Adverse events |  |  | x | x | x | x | x | x | x | x | x |
| Activity quetsionnaire |  | x |  |  |  |  |  |  |  |  |  |
| Muscle soreness |  |  |  | x | x | x |  | x | x | x |  |
| ACTIF pre |  |  | x |  |  |  | x |  |  |  |  |
| ACTIF post |  |  | x |  |  |  | x |  |  |  |  |
| SDMT |  |  | x |  |  |  | x |  |  |  |  |
| BDI-FS |  |  | x |  |  |  | x |  |  |  |  |
| Hand-grip-Strength-Test |  |  | x |  |  |  | x |  |  |  |  |
| VAS Fatigue after exercise |  |  | x |  |  |  | x |  |  |  |  |
| Cavi and SVA before injection |  |  | x |  |  |  | x |  |  |  |  |
| Cavi and SVA directly after exercise |  |  | x |  |  |  | x |  |  |  |  |
| Cavi and SVA 1 hour after exercise |  |  | x |  |  |  | x |  |  |  |  |
| **Exercise bout** |  |  | x |  |  |  | x |  |  |  |  |
|  |  |  |  |  |  |  |  |  |  |  |  |
| **Trial medication** |  |  |  |  |  |  |  |  |  |  |  |
| Anakinra |  |  | x |  |  |  | x |  |  |  |  |
| placebo |  |  | x |  |  |  | x |  |  |  |  |

| **Blood analysis** |  |  |  |  |  |  |  |  |  |  |  |
| --- | --- | --- | --- | --- | --- | --- | --- | --- | --- | --- | --- |
| IL-6 |  |  | x |  |  |  | x |  |  |  |  |
| GLP-1 (active) |  |  | x |  |  |  | x |  |  |  |  |
| Glucagon |  |  | x |  |  |  | x |  |  |  |  |
| Insulin |  |  | x |  |  |  | x |  |  |  |  |
| Glucose |  |  | x |  |  |  | x |  |  |  |  |
| IL-1Ra |  |  | x |  |  |  | x |  |  |  |  |
| GIP |  |  | x |  |  |  | x |  |  |  |  |
| CRP |  |  | x |  |  |  | x |  |  |  |  |
| TNF-a |  |  | x |  |  |  | x |  |  |  |  |
| Cortisol |  |  | x |  |  |  | x |  |  |  |  |
| GH |  |  | x |  |  |  | x |  |  |  |  |
| Retro Samples |  |  | x |  |  |  | x |  |  |  | x |
| CK |  | x | x |  |  |  | x |  |  |  | x |
| **Urinanalysis** |  | x |  |  |  |  |  |  |  |  |  |

